#### Functional MRI.

Both NS and motivational abnormalities reflect complex processes at a system level likely corresponding to functional brain activity within and between several regions and circuits [74]. To elucidate neural correlates of reward anticipation and processing, we will conduct functional magnetic resonance imaging (fMRI) at baseline and follow-up using an adapted version of Knutsson et al.’s [75] monetary incentive delay task (MIDT) as described in Nielsen et al. [76], and supplementing it by a social incentive delay task (SIDT), in which faces displaying different emotions [77] are used as feedback stimuli rather than varying amounts of money [cf. 78]. Comparing individuals with schizophrenia to healthy controls, meta-analysis of monetary reward-related blood oxygen level dependent (BOLD) signal changes has identified hypoactivation during reward anticipation in a network comprising the striatum, anterior and median cingulate cortex, amygdala, precentral gyrus, and superior temporal gyrus; while reward receipt was associated with hyperactivation of the striatum, insula, and amygdala, among others, and hypoactivation in the dorsolateral and medial prefrontal cortex [79]. NS severity has been found to specifically correlate with reduced reactivity of the ventral striatum to social, but not monetary rewards [80]. As the intervention targets social reward learning, we expect a normalisation of the neural response patterns to social rewards for participants in the intervention group.

#### Qualitative data.

Given the complex nature of negative symptoms and the study’s aim of investigating feasibility and acceptability of a novel therapeutic intervention, we will additionally employ qualitative methods to shed light on aspects of patients’ and therapists’ experiences that may remain undiscovered by means of quantitative analysis [81,82]. Semi-structured interviews with all patients in the intervention group will be conducted upon completion of the last therapy session, and a semi-structured group interview will be conducted with study therapists after all therapies have been finalised. Topics covered by the qualitative interviews will include the perceived usefulness, transferability, mechanisms of effect, and tolerability of the procedure. The qualitative investigation will also collect participants’ and therapists’ suggestions for improvement of the intervention.

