## Methods

### Study design

The study is sponsored by and conducted at Mental Health Centre Copenhagen, Mental Health Services, Capital Region of Denmark. In an assessor-blind, mixed-methods, randomised controlled trial (RCT), 30 participants with an SSD diagnosis (ICD-10 F2x) will be recruited from specialised outpatient care facilities for patients with SSD (so-called OPUS and F-ACT teams) within the Copenhagen Mental Health Services. Following an eligibility screening, participants will be randomly assigned to one of two study arms:

1) Treatment as Usual (TAU; control group) or2) TAU plus 10 sessions of VR-assisted psychotherapy (intervention group).

Clinical assessments, MRI, and data from seven-day Ecological Momentary Assessment (EMA, cf. “Secondary outcomes”) epochs will be obtained at baseline and upon treatment completion 14 weeks after baseline (see Fig 1).

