### Setting and procedure

The study is conducted by VIRTU Research Group at Mental Health Centre Copenhagen, Mental Health Services CPH, in collaboration with the Centre for Neuropsychiatric Schizophrenia Research (CNSR) at Mental Health Centre Glostrup, Denmark. MRI is performed at the Functional Imaging Unit (FIU), Rigshospitalet – Glostrup, Denmark.

Clinical, behavioural (EMA), and MRI data will be collected at baseline and at follow-up, 14 weeks after baseline, by a trained psychologist functioning as study assessor blinded to group allocation. Another psychologist will collect qualitative data on treatment acceptability (cf. “Qualitative data”).

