### Intervention

In addition to standard care, participants allocated to the intervention group will be offered 10 sessions of manualised, modularised, VR-supported psychotherapy delivered by licensed psychologists with expertise in working with VR-interventions for psychosis. A portion of each session will be spent in VR. Visual and auditory stimuli will be presented using the VR software Social Worlds [44] and VR Moodboost [45], which can be used to emulate a variety of real-life surroundings such as a park, a bus, a home, or a supermarket. Participants can virtually move around in these surroundings or engage in social interactions with avatars, whose voices are produced by real-time distortion of the therapist’s voice. The individually modified virtual reality scenarios are designed to stimulate social reward as operant conditioning principles, motivation and the experience of positive affect in the participant. Alongside the in-session experiences, the participant is given weekly activity tasks to be carried out at home between sessions. The participants are asked to register anticipatory pleasure before performing an in-session or at-home activity, and to register participatory pleasure directly after completing it.

The intervention is divided into four modules: Introduction, Motivation, Social Reward, and an extra module for individual adaptation (see the S2 File for a session overview of the ENGAGE VR therapy). Sessions on attention focus and motivating an avatar are adapted from Meins et al.’s [45] VR-SOAP intervention for social functioning in psychosis.

To bridge sessions and real-life behaviours, the weekly at-home activities will be planned using a study app [46]. In the study app, psychoeducational material on NS will be made available to participants in the intervention group after baseline assessment, and to participants in the control group after follow-up assessment. In-app graphs visualising the participant’s anticipatory and consummatory pleasure ratings of the in-session VR tasks and at-home activities will be used therapeutically to illustrate patterns in the participant’s experience of pleasure, such as biased discrepancies between anticipatory and consummatory pleasure, and patterns of development over the course of therapy, such as an increase in anticipatory pleasure.

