### Secondary outcome measures

#### Clinical, cognitive, and functional outcomes.

To obtain indications of a potential for treatment efficacy, clinical, cognitive, and functional outcomes, as presented in Table 2, will be assessed at baseline and at 14 weeks follow-up.

**Table 2 pone.0331632.t002:** Secondary clinical, cognitive and functional outcomes and measures.

Outcome	Measure	Data Source
Clinical assessment		
Severity of negative symptoms	Scale for the Assessment of Negative Symptoms [SANS, 47]	A
	Brief Negative Symptom Scale [BNSS, 48]	A
	Self-Evaluation of Negative Symptoms [SNS, 49]	S
Severity of positive symptoms	Scale for the Assessment of Positive Symptoms [SAPS, 50]	A
Interpersonal anhedonia	Anticipatory and Consummatory Interpersonal Pleasure Scale [ACIPS, 51]	S
Well-being	WHO-5 [52]	S
Depression	Calgary Depression Scale [CDSS, 53]	A
Cognitive assessment		
Defeatist beliefs	Defeatist Performance Attitude Scale [DPAS, 54]	S
Readiness for therapy	Readiness for Therapy Questionnaire [RTQ, 55]	S
Facial emotion recognition	Emotion Recognition Task [ERT, 56]	T
Functional assessment		
Daily life functioning	Personal and Social Performance Scale [PSP, 57]	A
	Social Functioning Scale [SFS, 58]	S
Intervention-related assessment		
VR immersion	Presence Questionnaire [59]	S
VR-induced motion sickness	Simulator Sickness Questionnaire [SSQ, 60]	S
Overall satisfaction	Client Satisfaction Questionnaire [CSQ, 61]	S

*Note.* A, assessor-rated; S, self-reported; T, test.

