#### Ecological momentary assessment (EMA).

Given their dynamic and fluctuating nature, capturing state NS is challenged by recall biases that may distort assessments based on retrospection [62]. EMA allows for capturing transient mental states with high temporal resolution and has previously been used to assess NS [63–65], yielding improved ecological validity [66] and allowing for fine-grained analysis of subcomponents of NS, such as anticipatory and consummatory anhedonia [67]. A specifically designed questionnaire will be issued to patients at five semi-random time points per day during two seven-day epochs at baseline (E1) and follow-up (E3). Participants will receive a notification on their phone, and the questionnaire will need to be completed within 15 minutes to be accepted. The questionnaire collects self-reported data concerning participants’ level of activity, affect, and company (see the S3 File for the complete EMA questionnaire and procedure). In between these high-frequency epochs (i.e., E1 and E3), a slightly altered version of the questionnaire will be issued each night, collecting the same data but referring to the entire previous day (E2).

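### As written, the intervention-only interview appears to come before the follow-up self-ratings, EMA epoch E3 and blinded assessment; the plan should place it after them

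*Protocol article*

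**What the plan says.** Under Qualitative data, the protocol article states: "Semi-structured interviews with all patients in the intervention group will be conducted upon completion of the last therapy session". The control arm has no counterpart. The content is described as follows: "Topics covered by the qualitative interviews will include the perceived usefulness, transferability, mechanisms of effect, and tolerability of the procedure". The same section adds that suggestions for improving the therapy will be collected.

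The outcomes have their own time anchors. Table 2 measures "will be assessed at baseline and at 14 weeks follow-up". Study design says that clinical assessments, MRI and EMA "epochs will be obtained at baseline and upon treatment completion 14 weeks after baseline". The EMA section places E3, a seven-day epoch, at follow-up.

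Two safeguards are stated. Follow-up data are collected "by a trained psychologist functioning as study assessor blinded to group allocation", whereas "Another psychologist will collect qualitative data on treatment acceptability" (both in Setting and procedure). Under Randomisation and blinding, participants are told not to disclose their arm to assessors.

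**The concern.** An outcome assessment should be preceded by the same study contacts in both arms, apart from the treatment itself. Here one arm appears to have an extra contact that is research procedure and not therapy: a conversation about usefulness, transfer to daily life and how the therapy works. These subjects lie close to what is then rated. Transfer to daily life is near the SFS and the EMA items on activity and company. Mechanisms are near the ACIPS and DPAS. The participants know their arm.

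Adjusting for baseline by ANCOVA cannot remove an influence that arises after randomisation in one arm only. A participant who has recently described the therapy at length may also be somewhat more likely to mention it to the blinded assessor.

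At stake are the efficacy signals. They are exploratory, but the Hypotheses section predicts superiority on negative symptoms and functioning, and the Discussion expects the data to support the design of a fully powered trial.

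**Working it through.** The plan gives no figure to reproduce on this point: the sample of 30 rests on pilot-study recommendations, without effect size, alpha or power. The check is mainly one of order.

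**1. The anchors side by side.**
- Interview: completion of the last therapy session (Qualitative data).
- Clinical battery and MRI: treatment completion, 14 weeks after baseline (Study design).
- E3: seven days at follow-up (EMA section), also placed at treatment completion by Study design.

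All three are tied to the end of therapy. No readable text says which comes first, and the schedule figure is not shown.

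**2. Two possible timelines.** The article states 10 sessions but not their spacing.
- *Weekly sessions* (an assumption suggested by the weekly home tasks): session 10 falls at about week 9 to 10. The gap to follow-up is 14 − 10 = 4 to 14 − 9 = 5 weeks, and the interview comes first.
- *Therapy runs to week 14*: the gap to the clinical battery is about zero and the order is open. For E3 it is less open. A seven-day epoch that begins once treatment is complete cannot be over when the last session ends. E3 could come first only if it overlapped the last week of therapy, and it would then not be a post-treatment measure, or if the interview were held well after the last session.

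**3. The calendar does not settle it.** Recruitment began on 9 January 2025 and follow-up on 7 April 2025. That is 88 days, or 88/7 = 12.6 weeks. Fourteen weeks from 9 January is 17 April. The nominal interval is therefore not exact, and the dates say nothing about order within the visit.

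**4. Which outcomes are open to influence.** Table 2 without the three intervention-related forms has 12 measures:
- assessor-rated, 5: SANS, BNSS, SAPS, CDSS, PSP;
- self-reported, 6: SNS, ACIPS, WHO-5, DPAS, RTQ, SFS;
- test, 1: ERT.

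The E3 questionnaire adds 5 × 7 = 35 self-report prompts per participant.

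**5. Illustration of size.** The documents give no value for an interview effect, so the shift δ is purely assumed. Take 15 per arm, no dropout, an unadjusted comparison in SD units and a two-sided 5% test:

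SE = √(2/15) = 0.365 SD

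false-signal rate = Φ(δ/SE − 1.96) + Φ(−δ/SE − 1.96)

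| Assumed δ (SD) | δ/SE | False-signal rate |
|---|---|---|
| 0 | 0 | 5.0% |
| 0.1 | 0.27 | 5.9% |
| 0.2 | 0.55 | 8.5% |
| 0.3 | 0.82 | 13.0% |

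The table shows what such shifts would do. It is not evidence that they occur.

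**The case against.** The strongest reply is that the sequence is inferred. Study design ties follow-up to treatment completion just as Qualitative data ties the interview to the last session, and visit order usually sits in the schedule and full protocol, which are not at hand. This stands, so the point can only say that the interview appears to come first. It does not remove the point, because the article does fix an anchor for the interview and that anchor, on its ordinary reading, precedes E3.

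A reader might infer more: that the intervention arm is primed and the efficacy signals are inflated. The documents do not support that.
- The direction is unknown. The interview also covers tolerability and asks for improvements, which invites criticism as much as praise.
- The arm is unblinded and is offered ten sessions with repeated pleasure ratings and in-app graphs. Any expectancy effect is largely there already, and one interview adds little that could be separated from it.
- On the weekly timeline the interview lies 4 to 5 weeks before the ratings, not immediately before them.
- Expressing an assumed shift as a share of an assumed true effect would give a ratio of two guesses.
- Not all 15 participants need reach the interview; the trial's own retention criterion is 70%.

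On unblinding, the separate interviewer and the non-disclosure instruction already limit the risk, and a slip could equally come from the therapy itself. Prompt interviewing also has merit, since acceptability is a primary aim and recall is fresher. These arguments lower the weight of the point. They do not give a reason to leave an avoidable one-arm contact ahead of the outcomes.

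**Conclusion.** The point holds in limited form. The text as written appears to put an intervention-only conversation about usefulness and mechanisms before the follow-up self-ratings, E3 and the blinded assessment. The reading is firm for E3 if E3 is a post-treatment measure. For the clinical battery it is likely but not certain.

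The effect is unknown in size and direction and probably small beside the therapy. It touches secondary, exploratory comparisons: mainly the six self-reported measures and the EMA items, and the five assessor-rated measures only indirectly. I make no claim about the primary satisfaction rating, because the readable text does not say when it is taken. The point deserves a change because the imbalance comes from scheduling, not from the treatment, and is cheap to remove.

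**What to change.** In Qualitative data, replace the timing with wording such as: *Participant interviews will be held as soon as possible after the week-14 assessment and EMA epoch E3 are complete, or at withdrawal for participants who leave early.* Keep the topics and the separate interviewer. The withdrawal clause keeps early leavers from going uninterviewed.

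Recruitment and follow-up had already begun. For participants interviewed before their follow-up, record the order and report it as a limitation. An analysis with and without them is not a general remedy: if every intervention participant was interviewed first, leaving them out removes the arm. If outcomes already come first in practice, correcting the sentence is enough.

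The cost is later recall of the sessions. If therapy ends at week 14, the delay is about the length of the follow-up window, roughly the seven days of E3. If sessions are weekly without gaps (assumed), it is 4 to 5 weeks and up to a further week for E3. No extra staff or change to the therapy is needed, and the interview need not add a visit if it is held at the close of follow-up.

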### Data analysis

#### Statistical analysis.

Feasibility and acceptability of trial procedures will be assessed by calculating proportions and 95% exact Clopper Pearson confidence intervals for recruitment, treatment retention, and satisfaction with therapy.

Signals of treatment efficacy will be explored by comparing secondary outcome measures between the control (TAU) and intervention (TAU + VRT) groups using analysis of covariance (ANCOVA), adjusting for baseline scores. EMA data will be analysed employing multilevel linear modelling (MLM).

### Data management

The study, including all technical solutions, will comply with the General Data Protection Regulation (GDPR). Assessors conducting interviews with the participants will enter the data directly into an electronic case report form (CRF) using REDCap. When necessary, the data will be collected on paper and later entered in REDCap. Each participant’s data is connected to a unique serial number, and only assigned researchers have access to the data in REDCap. Questionnaires can be directly sent from REDCap to the secure public Danish mailing system (Digital Post) that is connected to each citizen’s personal identification number (CPR), and completed forms are returned digitally.

Data on paper, consent forms and other physical material with personal information are stored locally behind double locks. Imaging data and audio recordings will be saved on a logged network drive controlled by the Capital Region of Denmark, Centre for IT and Medical Technology (CIMT), granting only assigned researchers and therapists involved in the study access to the files.

### Ethics

The study has been approved by the National Committee on Health Research Ethics for the Capital Region of Denmark (H-24046055; date of approval for study protocol, 6 September, 2024; date of approval for revised study protocol, 15 April, 2025). Informed consent will be obtained from all participants after they have been given oral and written information about the study. Compliant with pertinent regulations and as approved by the Health Research Ethics Committee, no specific procedure will be employed to determine participants’ capacity to provide consent. However, if study staff are in doubt concerning a participant’s capacity to consent, case-to-case decisions will be made by the study’s Principal Investigator. Participants are informed that participation is voluntary and that they can withdraw from the study at any time without adverse consequences to their treatment by the Mental Health Services. Side effects and adverse events will be monitored and documented throughout the study period, and any adverse events assumed to be related to the study will be reported to the Committee on Health Research Ethics of the Capital Region of Denmark. Aside from occasionally reported transient cybersickness [83], no adverse events are expected in direct relation to VRT.

### Study status

Recruitment of participants started 9 January, 2025, and is expected to end by 30 September, 2025. Follow-up data collection started 7 April, 2025, and is projected to be completed by 31 December, 2025. Results are expected by 31 May, 2026.

## Discussion

Existing psychosocial treatments for SSD have demonstrated some efficacy in reducing NS, yet effect sizes remain generally small [9], and few interventions are specifically designed to target NS directly [22]. Proposed mechanisms underlying NS include abnormalities in reward processing, dysfunctional beliefs, and impairments in social cognition – each offering pertinent targets for intervention [74]. The present study aims to evaluate the feasibility and acceptability of a novel, symptom-specific, psychological intervention that specifically leverages social reward learning for reducing NS through VR technology, which has proven safe and efficacious in treating psychotic symptoms of psychosis [35].

This study has several strengths. First, it builds on a sound psychological rationale and integrates immersive VR to provide a realistic yet controlled environment for engaging the motivational system in ecologically valid scenarios. Second, it comprises a broad range of clinical, biological, behavioural, and qualitative outcomes, allowing for a multidimensional analysis of feasibility, acceptability, and signals of efficacy and mechanisms of change. Third, service users with lived experience were involved from the outset in shaping the intervention, enhancing its relevance and acceptability. Fourth, the controlled, assessor-blinded design of the study supports methodological rigor, creating robust groundwork for a potential follow-up efficacy trial.

A key limitation is the absence of an active control group. Instead, the intervention is compared to TAU without systematic assessment of its content or intensity. Given the heterogeneity of TAU, this may introduce variability that could affect outcomes [84]. This limitation, however, appears acceptable within the context of a pilot study.

In sum, this pilot study will assess the feasibility and acceptability of a VR-based intervention addressing NS in patients with SSD. If successful, it will provide critical data to support the design of a fully powered randomised clinical trial and contribute to the development of more effective treatments for these persistently disabling symptoms.
